#### Qualitative Data Analysis

Thematic analysis will be applied to the interview transcripts, following the methodology proposed by Braun and Clarke [34]. The CFIR framework will guide the coding process and the organization of emerging themes [35]. Analysis will be conducted using Excel as an analytic workspace. The process will begin with close reading and familiarization, followed by a deductive coding phase that maps participants’ responses onto the relevant CFIR domains and constructs. This approach supports a structured interpretation of barriers and facilitators, while also allowing room for emerging contextual elements.

#### Quantitative Data Collection and Analysis

In parallel with each interview, participants will complete the EBPAS-36, a validated instrument that assesses attitudes toward adopting evidence-based practices. In line with the rolling baseline design, T1 and T2 are scheduled approximately 6 and 12 months after each participant’s baseline assessment.

The EBPAS-36 consists of 36 items rated on a 5-point Likert scale and includes multiple subscales. Descriptive statistics will be calculated for each wave of data collection, including mean scores and SDs. Negative subscale items will be reverse-coded so that higher scores consistently indicate more positive attitudes toward innovation and structured clinical practices.

Repeated measures will be analyzed using a descriptive longitudinal approach. For participants providing data at multiple time points, changes in EBPAS-36 total and subscale scores will be explored within individuals, focusing on the direction and magnitude of change across waves. Where appropriate and depending on data completeness and distributional assumptions, nonparametric paired comparisons (eg, Wilcoxon signed rank tests) may be used to explore differences between time points. These analyses are intended to be exploratory and supportive of the qualitative findings, rather than hypothesis testing.

Quantitative data will be linked to the corresponding qualitative data at the level of individual participants. This integration will enable a dual-layered analysis of each psychotherapist’s experience, combining narrative accounts with attitudinal profiles. Although not intended as a formal triangulation, this approach will enhance the interpretive depth of the study and contribute to a deeper understanding of implementation trajectories over time.

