#### Qualitative Data Collection

Semistructured interviews will be conducted with a sample of around 30 psychotherapists, selected to reflect the diversity of the Italian context in terms of employment setting (private, public, freelance), therapeutic orientation, and geographical location. Recruitment is carried out within the broader OutProFeed project through established collaborations with psychotherapy training schools and their professional networks, complemented by outreach to practitioners in both private practice and organizational settings. The research team monitors the evolving sample composition during enrollment to avoid overrepresentation of specific profiles (eg, a single orientation or geographic area) and to ensure coverage across the predefined variation dimensions. This recruitment approach is intended to reduce selection bias while remaining consistent with the study’s purposive, maximum-variation design. While an initial target of approximately 30 participants is set, the final sample size will be determined during the research process. Data collection will continue until all these key dimensions are represented and data saturation is reached.

The target sample of approximately 30 psychotherapists is grounded in the structural and professional heterogeneity of psychotherapy practice in Italy. In particular, the sampling strategy is designed to ensure coverage of the main psychotherapeutic orientations currently practiced in the Italian context, which represent distinct clinical traditions and professional cultures that may shape how ROM is interpreted and integrated into everyday practice. The study aims to include psychotherapists from at least five widely adopted approaches (eg, cognitive-behavioral, psychodynamic, systemic-relational, humanistic, and integrative orientations).

Within this framework, participants are purposively recruited to also reflect variation in employment arrangements (private practice and organizational settings) and geographic macro-areas (North, Center, South/Islands). With a target of approximately 30 participants, the study can include multiple psychotherapists within each major orientation while preserving sufficient diversity across organizational and regional contexts. This sample size supports comparative, process-oriented analysis of implementation trajectories across different professional logics, without aiming for statistical representativeness.

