#### Data Integration

Qualitative and quantitative data are integrated at the level of individual participants using a convergent, case-oriented mixed methods approach. For each psychotherapist, interview data constitute the primary source for reconstructing the implementation process and its evolution over time. EBPAS-36 scores are used as complementary information to characterize psychotherapists’ attitudinal positioning toward evidence-based practices at each time point and to support the interpretation of qualitative changes or continuities. Integration, therefore, occurs through iterative comparison within cases, examining how shifts in narratives of ROM integration relate to stable or changing attitudinal profiles. This strategy prioritizes explanatory coherence over formal triangulation and is aligned with the study’s focus on understanding implementation as a situated professional process.

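### Individual EBPAS-36 change is read by direction and size and set against the interviews, with nothing to separate change from measurement error (a minor, interpretive point)

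*Protocol article*

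**What the plan says.** The protocol article gives the EBPAS-36 to each participant three times: "T1 and T2 are scheduled approximately 6 and 12 months after each participant’s baseline assessment". On the instrument it says: "The EBPAS-36 consists of 36 items rated on a 5-point Likert scale and includes multiple subscales". It gives no subscale lengths, no reliability and no expected SD.

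Under Quantitative Data Collection and Analysis there are two levels of reading. At group level there are means and SDs per wave, and optionally a test: "nonparametric paired comparisons (eg, Wilcoxon signed rank tests) may be used to explore differences between time points". At individual level, "changes in EBPAS-36 total and subscale scores will be explored within individuals, focusing on the direction and magnitude of change across waves". The status of all this is stated plainly: "These analyses are intended to be exploratory and supportive of the qualitative findings, rather than hypothesis testing".

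Data Integration carries the individual reading into the case analysis. There, "EBPAS-36 scores are used as complementary information to characterize psychotherapists’ attitudinal positioning toward evidence-based practices at each time point", and integration proceeds by "examining how shifts in narratives of ROM integration relate to stable or changing attitudinal profiles".

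On numbers, Qualitative Data Collection says: "While an initial target of approximately 30 participants is set, the final sample size will be determined during the research process".

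**The concern.** Speaking of one therapist's profile as stable or changing requires some view of how large a difference must be before it counts as change. The only features the article names are direction and magnitude. It mentions no standard error of measurement, reliability or minimum change.

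A questionnaire score contains error on every occasion, and the difference of two scores contains it twice. Someone whose attitude has not moved will therefore usually show some rise or fall. When that movement is laid beside an interview, a chance rise that fits the account can be taken as support for it, and a chance fall can be explained away. The group summaries do not help, because integration is done person by person.

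The article is itself cautious about this instrument in small numbers. Under Pilot Test it explains that the EBPAS-36 was withheld from the three pilot participants because it needs a large enough and varied enough sample to be meaningful. Reading it one case at a time sits uneasily with that caution.

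At stake are case-level remarks linking an attitude shift to the integration of outcome monitoring, not the study's main result.

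**Working it through.** The article states no figure on this point, so there is none to reproduce. What follows is an illustration.

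**Inputs**
- From the article: about 30 participants and three waves.
- Assumed: reliability r of 0.7, 0.8 or 0.9, the same at each wave; normally distributed errors, independent between waves; no true change in anyone. Changes are expressed in units of the between-person SD at T0.
- Chosen for illustration: a shift of 0.5 SD.

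**Step 1. Spread of a change score when nothing has changed.** SD of the difference = √(2(1 − r)).
- r = 0.7: √0.6 = 0.775
- r = 0.8: √0.4 = 0.632
- r = 0.9: √0.2 = 0.447

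**Step 2. Apparent shift beyond 0.5 SD from error alone.** Probability = 2 × (1 − Φ(0.5 / SD of difference)).

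| r | 0.5 / SD of difference | Probability | Of 30 people |
|---|---|---|---|
| 0.7 | 0.645 | 52% | 15.6 |
| 0.8 | 0.791 | 43% | 12.9 |
| 0.9 | 1.118 | 26% | 7.9 |

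These figures are for one score and one pair of waves. Reading several subscales adds further chances of an apparent shift. At r = 0.6 the probability is 58%.

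**Step 3. Direction alone.** With no true change, rises and falls are about equally likely. Of the 6 orderings of three waves, 2 run steadily up or steadily down, so a consistent trend appears by chance in 2/6 = one third, about 10 of 30 (ties ignored). If the true change is 0.3 SD, the observed direction is wrong with probability 1 − Φ(0.3 / SD of difference): 35%, 32% and 25% at r = 0.7, 0.8 and 0.9.

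**Step 4. The 95% reliable-change limit.** 1.96 × √2 × SD_T0 × √(1 − r) gives 1.52, 1.24 and 0.88 SD.

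**Step 5. What that limit does.**
- With no true change, 5% of people still exceed it: 30 × 0.05 = 1.5 expected per score and comparison. The chance of at least one is 1 − 0.95^30 = 0.79.
- With a true change of 0.5 SD, the chance of exceeding it in either direction is about 10%, 12% and 20%. For example, at r = 0.9: 1 − Φ((0.877 − 0.5) / 0.447) = 1 − Φ(0.84) = 0.20, and the other tail adds only about 0.001.

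Step 5 is why a change inside the limit should not be called stable. Most modest real changes would fall there too.

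**The case against.** The strongest reply is that the article contains no error. It says changes are explored, and attention to magnitude is compatible with an error band. A full protocol or analysis plan, not shown, could hold such a rule. That stands as a limit on severity. The point remains that the article does state how individual change is read and what it is compared with, and that reading makes no allowance for error.

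A reader might go further and infer that therapists will be formally classified as changed or stable on raw differences, so that noise becomes a result. The text does not support this. It gives no cut-off and no classification rule. The scores are complementary to the interviews, and formal triangulation and hypothesis testing are both disclaimed.

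A reader might also infer that the only group-level output is a p value. That is not so either. Means and SDs are planned at each wave, magnitudes are to be examined, and the Wilcoxon test is optional.

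Nor can it be asserted from the article that the subscales are short or unreliable; it says only that there are several. The percentages above therefore depend on the assumed reliability and on an illustrative 0.5 SD mark that the plan does not use.

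Finally, a hard label at the reliable-change limit would miss 80% to 90% of people with a true 0.5 SD change. This objection is sound, and the fix is shaped by it.

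**Conclusion.** The point holds in a limited form. Read as written, the two sections would let measurement error pass for attitudinal change in a material share of cases: about 26% to 52% of people beyond 0.5 SD at assumed reliabilities of 0.9 down to 0.7, per score and pair of waves. This rests on the classical error model and on a reliability that the article does not give. It is a minor weakness of interpretation. Interviews remain the primary source, the scores are exploratory, and no primary conclusion, error rate or sample size depends on them.

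**What to change.** In Quantitative Data Collection and Analysis and in Data Integration:

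1. Report each participant's change in total score with a reliable-change band, ± 1.96 × √2 × SD_T0 × √(1 − reliability), using the study's own T0 SD. Show it over a plausible range of reliabilities, because about 30 people estimate reliability imprecisely. Internal consistency also misses error that varies from one occasion to the next over 6 to 12 months.
2. Describe a change inside the band as not distinguishable from measurement error, rather than as stable, and do not use it as support for a shift in the narrative.
3. Keep subscale changes descriptive.
4. If the Wilcoxon test is used, give beside it the Hodges-Lehmann estimate (the pseudomedian of the paired changes) with its 95% confidence interval.

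The cost is some wording and a few lines of code; no new data are needed. The Results section says that no implementation outcome analyses had been completed at submission, and the abstract places analysis after follow-up ends, so the rule can be set before results are seen. The price is that fewer therapists can be described as changed, and modest true changes will be left indeterminate.

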#### Data Integration

Qualitative and quantitative data are integrated at the level of individual participants using a convergent, case-oriented mixed methods approach. For each psychotherapist, interview data constitute the primary source for reconstructing the implementation process and its evolution over time. EBPAS-36 scores are used as complementary information to characterize psychotherapists’ attitudinal positioning toward evidence-based practices at each time point and to support the interpretation of qualitative changes or continuities. Integration, therefore, occurs through iterative comparison within cases, examining how shifts in narratives of ROM integration relate to stable or changing attitudinal profiles. This strategy prioritizes explanatory coherence over formal triangulation and is aligned with the study’s focus on understanding implementation as a situated professional process.

### Pilot Test

A pilot phase was conducted with 3 psychotherapists to assess the adequacy and feasibility of the data collection protocol and to support its refinement prior to the main study. This pilot phase was explicitly conceived as a feasibility and protocol-refinement step and not as a source of empirical findings or preliminary implementation results. It provided a pragmatic opportunity to test the interview guide developed around the selected CFIR constructs (Table 1) and to assess the clarity, flow, and acceptability of the interview structure and language.

The interview guide used during the pilot is available in Multimedia Appendix 2. An initial version had been prepared based on the selected constructs. Insights from the pilot led to minor procedural refinements, primarily concerning the sequencing and phrasing of questions to facilitate a more natural conversational flow consistent with clinical interaction. The substantive content of the questions was not altered, and all targeted constructs were retained.

Quantitative data were not collected at this stage. The EBPAS-36 questionnaire, which will be administered in the main phase of the study, is a validated instrument that requires a sufficiently large and diverse sample to yield meaningful results. Given the feasibility-oriented purpose of the pilot and the small number of participants involved, its administration at this stage was not considered appropriate.

### Ethical Considerations

The study has been reviewed and approved by the Committee for Integrity and Research Ethics of the University of Bergamo (2024_04_08) in compliance with national regulations and the Declaration of Helsinki. All participants are informed about the aims of the research, the voluntary nature of their participation, and the possibility to withdraw at any time without consequences.

Before each interview, participants receive an information sheet and are asked to provide written informed consent, including permission to record the session. Consent forms are stored securely and separately from the collected data. Interviews are conducted in a confidential setting using secure online platforms. Audio recordings are transcribed verbatim and anonymized to ensure participant privacy.

All personal identifiers are removed or replaced with pseudonyms during transcription. Data are stored in encrypted, password-protected institutional folders accessible only to the research team. Files are regularly backed up and managed in accordance with institutional data protection policies and the European General Data Protection Regulation.

For psychotherapists operating in private practice and using the digital platform, the implementation study does not involve access to identifiable patient-level clinical data. The research team does not access or extract raw clinical content entered into the platform. Data collected for research purposes focus exclusively on psychotherapists’ experiences, attitudes, and implementation processes and are analytically and technically separated from any clinical documentation generated within routine practice.

Quantitative data collected through the EBPAS-36 questionnaire are similarly anonymized and securely stored. The integration of qualitative and quantitative data at the individual level is performed using anonymized study codes, ensuring that no identifying information is used in the analysis or dissemination of findings.

Dissemination of results will take place in aggregated form only, and no individual participant will be identifiable in publications or presentations. Participants are also informed that the results may contribute to academic and policy-oriented outputs aimed at improving clinical practice in the field of psychotherapy. No participant compensation is provided.

## Results

This implementation study is conducted within the broader OutProFeed project, which received ethical approval from the Ethics Committee of the University of Bergamo in April 2024 (protocol number 2024_04_08); the present work is a predefined substudy covered by this approval. Technical setup of the digital platform and engagement with participating psychotherapists were conducted between May and November 2025. Baseline (T0) implementation data collection started on a rolling basis in December 2025 and is planned to continue through March 2026. The midimplementation follow-up (T1; approximately 6 mo after individual baseline) is expected to take place between June and October 2026, with the final follow-up (T2; approximately 12 mo after baseline) planned between December 2026 and April 2027. As of the time of manuscript submission, no implementation outcome analyses have been completed.

## Discussion

### Main Contributions and Anticipated Insights

This implementation study is designed to generate practice-relevant insights into how digitally supported ROM is incorporated into routine psychotherapy work in a fragmented and professionally autonomous care system. Specifically, we expect to identify (1) the implementation mechanisms through which psychotherapists interpret, negotiate, and integrate ROM into existing clinical routines, (2) the contextual and organizational conditions that enable or constrain this integration, and (3) how these dynamics vary across therapeutic orientations and practice arrangements. These anticipated contributions are implementation-focused and do not concern clinical effectiveness, which is addressed within the broader OutProFeed trial.

ROM and feedback-informed approaches are supported by a robust body of evidence demonstrating their potential to improve clinical outcomes, patient engagement, and early detection of treatment deterioration [2,6,7]. Despite this evidence, the integration of ROM into routine psychotherapeutic practice remains uneven, particularly in settings where its use requires sustained changes to psychotherapists’ workflow, documentation practices, and interaction with patients [3,5,9]. Research on the digital transformation of mental health services further suggests that digital platforms can lower some practical barriers to ROM adoption but do not in themselves resolve deeper professional and organizational challenges related to implementation [10]. In this context, the present protocol explicitly focuses on implementation as a professional and organizational process, rather than on clinical effectiveness, which is addressed within the broader OutProFeed trial.

Despite the evidence base, ROM adoption in psychotherapy is often hindered by barriers that are well documented in implementation and measurement-based care research. These include psychotherapists’ concerns that structured monitoring may constrain clinical discretion or undermine therapeutic work, uncertainty about data ownership and potential “surveillance” uses of outcome data, and perceived workload associated with repeated administration and review of measures [3,5,6,9]. In digitally mediated models of care, technology can reduce friction in data capture and feedback, but it can also amplify sensitivities related to confidentiality, governance, and professional autonomy if the tool is perceived as externally imposed or poorly aligned with clinical routines [10]. These barriers are expected to be particularly salient in fragmented systems dominated by independent private practice, such as Italy, where formal organizational mandates and shared infrastructures are limited [18,21].

### Relation to Prior Implementation Research

From an implementation science perspective, this study responds to recent calls to strengthen mental health implementation research by attending more closely to contextual variation, professional practices, and the dynamics of early-stage implementation [26]. The Italian psychotherapy ecosystem offers a particularly salient empirical setting for this purpose. Psychotherapy in Italy is characterized by high professional autonomy, strong theoretical pluralism, and limited institutional coordination, with service provision largely fragmented across private practice and under-resourced public services [18,21]. In such a context, the uptake of structured monitoring practices such as ROM is likely to depend less on formal mandates or technical availability and more on how these practices are perceived to fit with psychotherapists’ professional identities, therapeutic orientations, and everyday clinical routines.

Consistent with this view, the study conceptualizes implementation as an evolving process of professional integration rather than as a binary outcome of adoption versus nonadoption. Preliminary insights from the pilot phase suggest that variability across therapeutic orientations and practice arrangements is not incidental but central to understanding how ROM is interpreted and enacted in practice. This aligns with implementation research emphasizing nonlinear and processual models of change, in which innovations are adapted, negotiated, and selectively incorporated into routine work over time. The use of the CFIR provides a structured analytical lens to identify multilevel determinants of these processes while enabling comparison with prior implementation studies in digital mental health and psychotherapy [27,28].

